### Secondary outcomes

The following secondary outcomes will also be assessed at 24 months of life:

•Multiorgan dysfunction (adverse events in three or more organ systems),

•Bilateral sensorineural hearing loss more than 40 dB

•Epilepsy (recurrent seizures beyond the neonatal, period requiring anticonvulsant treatment)

•Developmental delay

•Multiple Disabilities (epilepsy, cortical visual impairment, sensorineural hearing loss, developmental delay)

Finally, the neuroradiologic outcome will be assessed by comparing the imaging obtained by standard cerebral MRI, DTI and spectroscopy performed within the first 7 days, at 3 months and 18 months of age. Brain injuries will be classified as isolated lesions of the white matter (WM), of basal ganglia and thalami (BGT), with or without involvement of the posterior limb of the internal capsule (PLIC), of cortex (COR), or various combinations of such lesions
[65].

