## Background

### Neonatal hypoxic-ischemic encephalopathy: disease incidence and pathogenesis

In countries with a high level of perinatal care, the incidence of asphyxia responsible for moderate or severe encephalopathy is 2–3 per 1000 term infants
[1,2]. The ensuing encephalopathy may present with need for resuscitation at birth, neurological depression, seizures or electroencephalographic (EEG) abnormalities. Hypoxic ischemic encephalopathy (HIE) is still the leading cause of perinatal mortality and severe neurological impairment. Mortality rate is 10% for moderate and 60% for severe HIE. About 30% of survivors with moderate and 100% with severe HIE exhibit permanent neurological disability
[3,4].

Encephalopathy results from the combination of reduced cerebral oxygenation (hypoxemia) and/or reduced perfusion (ischemia). Cerebral damage develops in two distinct phases. During the acute phase neuronal death occurs by necrosis of neuronal cells, a result of a rapid depletion of brain energy. However, after a few hours, cerebral energy metabolism recovers, but a cascading series of biochemical events triggers neuronal apoptosis and leads to severe brain damage. These events include an increased release of excitatory neurotransmitters, especially glutamate
[5]. Glutamate acts on three classes of receptors that control the passage of ion channels through the neural cell membrane: alpha-amino-3-hydroxy-5-methyl-4-isoxazolepropionate (AMPA), kainate and *N*-methyl-D-aspartate (NMDA) receptors. Neurons (and glia) contain high concentrations of glutamate, which is usually released in small amounts and for short periods of time (milliseconds)
[6]. Exceedingly high glutamate concentrations can over-excite nervous cells and lead to their death (excito-toxicity)
[7]. This excito-toxicity contributes to neuronal damage in various neurodegenerative disorders.

Glutamate activates AMPA receptors, depolarizes the cell and promotes the removal of the voltage-dependent block operated by Mg^++^[8,9] on NMDA receptors: this promotes the entry of Ca^++^ through this channel
[10]. Calcium entry stimulates in turn a series of processes that lead to necrosis and apoptosis. These processes include the Ca^++^ overload in the mitochondria, responsible for the production of free radicals
[6,11-13]; the activation of caspases and the release of factors inducing apoptosis

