#### Neuroradiologic follow-up

Standard cerebral magnetic resonance imaging (MRI), diffusion tensor imaging (DTI) and spectroscopy will be performed at the end of the hypothermic treatment within the first week, at three months and at 18 months.

Neuroradiologists responsible of follow-up will be blindfolded about which newborns have been treated with TPM in addition to hypothermia.

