### Experimental plan and data analysis

Based on the medical literature, the mean incidence of the combined frequency of mortality and severe neurodevelopmental disability in survivors at 18 months of age is approximately 50%. In fact this percentage is 55% in the cool Cap study
[66], 44% in the NICHD study
[68], 45% in the TOBY trial
[69], 51.4% in the ICE trial
[70], and 50.9% in the neo.nEURO.network study
[71]. We hypothesize that treatment with TPM may reduce the incidence of the combined frequency of mortality and severe neurodevelopmental disability in survivors at 18 months at 15%. In order to compare the incidence of this primary outcome between newborns receiving TPM plus hypothermia (treated) and those only receiving hypothermia (control group), the estimated sample size was calculated, considering normal distribution, an alpha error of 0.05 and a power of 80 percent. The sample size for each group is 32 participants.

The three units have an overall admission rate of approximately 10 term newborns with HIE per year. Due to the high hypothetical advantages of this treatment, we estimate 90-100% rate of consent and we predict we would recruit the 64 newborns over around 24 months period with a realistic safety margin.

Mortality, the incidence of severe neuromotor disability, cortical vision, sensorineural hearing loss, developmental delay, epilepsy will be evaluated at 18 months of life.

To evaluate TPM safety, cardiac and respiratory parameters (heart frequency, blood pressure, oxygen saturation, respiratory support), will be continuously monitored. Blood samplings will be performed to check renal, liver and metabolic balance. Kruskal-Wallis test will be used to assess possible differences between newborns treated or not with TPM. The safety will be also evaluated by means of relative risk (RR)
[132]. RR will be calculated as the ratio between the probabilities of side effects in the TPM group with respect to the control group. Values of RR lower than 1, will be associated to the efficacy of the treatment.

Finally, we will evaluate the different distribution of any brain lesions on MRI brain highlighted.The RR is calculated for each item studied. An RR <1 indicates an improvement of neurological, neurodevelopmental and neuroradiologic hypothermia due to the association-topiramate.

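### Secondary disability items and the 3- and 18-month MRI can be observed only in infants alive at assessment, yet any relative risk below 1 is read as improvement regardless of mortality

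*Protocol article*

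**What the plan says.** The Primary outcome section of the protocol article combines death with severe disability. The Secondary outcomes section does not. It introduces hearing loss, epilepsy, developmental delay and multiple disabilities with "The following secondary outcomes will also be assessed at 24 months of life", and adds a comparison of MRI lesion patterns. Under Neuroradiologic follow-up, the scans "will be performed at the end of the hypothermic treatment within the first week, at three months and at 18 months".

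The section Experimental plan and data analysis fixes the measure: "The RR is calculated for each item studied". It then says that an RR below 1 shows that adding topiramate improved neurological, neurodevelopmental and neuroradiologic results. That reading carries no condition. Mortality is listed in the same section among the items evaluated at 18 months, but nothing links the reading of the other RRs to it. The article does not say whether the denominator is survivors or all randomised infants.

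The Background states "Mortality rate is 10% for moderate and 60% for severe HIE", with permanent disability in about 30% of survivors of moderate HIE and 100% of survivors of severe HIE.

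**The concern.** An infant who dies before an assessment cannot show epilepsy, delay, hearing loss or a late MRI lesion. That infant is either dropped (survivor denominator) or counted as free of the event (all-randomised denominator). On the Background rates, the infants most likely to die are also those most likely to be disabled if they live. An effect on survival can therefore look like an effect on injury, in either direction.

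Comparing neurological and neuroradiologic outcome between the arms is the second of the two major objectives. In a pilot of 64 infants these item-by-item results are likely to shape how the trial is read. A rule that calls every RR below 1 an improvement could report benefit where disabled survivors had only become deaths.

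**Working it through.** **The plan's own figure.** The sample size rests on the primary composite: a control rate "in survivors at 18 months of age is approximately 50"%, a treated rate "in survivors at 18 months at 15"% (read as *to* 15%), and "an alpha error of 0.05 and a power of 80 percent" (two-sided assumed). With mean rate 0.325:

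- n = [1.96·√(2·0.325·0.675) + 0.842·√(0.5·0.5 + 0.15·0.85)]² / 0.35² = 26.9
- with continuity correction: (26.9/4)·[1 + √(1 + 4/(26.9·0.35))]² = 32.4, so 33

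This is within one infant of the article: "The sample size for each group is 32 participants". The point below does not change it.

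**Inputs for the illustration.** From the Background: mortality 10% (moderate) and 60% (severe); disability among survivors 30% and 100%. Assumed: 16 moderate and 16 severe infants per arm; topiramate raises severe mortality to 80% and does nothing else.

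| | Control | Topiramate |
|---|---|---|
| Deaths, moderate | 16 × 0.10 = 1.6 | 1.6 |
| Deaths, severe | 16 × 0.60 = 9.6 | 16 × 0.80 = 12.8 |
| Total deaths | 11.2 | 14.4 |
| Survivors | 20.8 | 17.6 |
| Disabled, moderate | 14.4 × 0.30 = 4.32 | 4.32 |
| Disabled, severe | 6.4 × 1.00 = 6.4 | 3.2 × 1.00 = 3.2 |
| Total disabled | 10.72 | 7.52 |
| Disabled / survivors | 51.5% | 42.7% |
| Death or disability | 21.92 of 32 | 21.92 of 32 |

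- Death RR = 14.4/11.2 = 1.29
- Composite RR = 21.92/21.92 = 1.00
- Disability RR among survivors = 42.7/51.5 = 0.83
- Disability RR over all randomised = 7.52/10.72 = 0.70

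**Where the survivor figure comes from.** Within the moderate stratum disability is 30% in both arms, and within the severe stratum 100% in both, so each stratum RR is 1.00 and so is the Mantel-Haenszel RR. The 0.83 arises from pooling strata whose mix differs among survivors.

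**Rates nearer to cooled infants.** Multiply the four Background rates by 0.81, the meta-analysis risk ratio quoted in the article, and again add 20 points to severe mortality (48.6% to 68.6%).

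- 16 moderate, 16 severe: control 10.23/22.93 = 44.6%; topiramate 7.64/19.73 = 38.7%; survivor RR 0.87.
- 22 moderate, 10 severe: control 9.08/25.36 = 35.8%; topiramate 7.46/23.36 = 31.9%; survivor RR 0.89. The control composite is (6.64 + 9.08)/32 = 49%, close to the planned 50%.

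**Dependence on who dies.** With the unscaled rates, a severe share of 30% to 70% and 5 to 15 percentage points of extra deaths:

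- Deaths random among would-be survivors: survivor RR 1.00, all-randomised RR 0.73 to 0.93.
- Deaths only among infants who would not have been disabled: survivor RR above 1, all-randomised RR 1.00.

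**The reverse case.** At 16/16 with the unscaled rates, lower severe mortality from 60% to 40%. Disabled: 4.32 + 9.6 = 13.92 of 24 survivors (58.0%). The survivor RR is 58.0/51.5 = 1.13 and the all-randomised RR 13.92/10.72 = 1.30, although deaths fall from 11.2 to 8.0.

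**The case against.** **Stratification removes the example.** Randomisation is stratified by aEEG into moderate and severe, and a stratified survivor RR in the illustration is exactly 1.00. Whether the RR is stratified is a detail an article may leave to the full protocol or analysis plan. This stands for the survivor denominator. It does not rescue the reading rule: deaths can still be selective within a stratum, and counting deaths as no event lowers the RR even when extra deaths are random.

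**The direction is not certain.** A reader might infer that any rise in mortality must show up as less disability. The documents do not support that: it depends on who dies and on a denominator the article does not give. The unstated denominator is not itself the fault; the stated reading of every RR below 1 is.

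**The size rests on assumptions.** No section gives the moderate/severe mix or suggests a 20-point rise in mortality, and the unscaled 16/16 example has a control composite of 21.92/32 = 68.5% against a planned 50%. This stands, and the scaled figures of 0.87 and 0.89 are the better guide.

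**Mortality is reported anyway.** It is a listed item, and the primary outcome counts it. But nothing makes the other RRs conditional on it, and a difference of this size would raise no alarm: 14 against 11 deaths of 32 gives a Fisher p of about 0.61.

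**Death-inclusive items are diluted.** With 11.2 deaths of 32 in both arms, halving an impairment from 15% to 7.5% of 20.8 survivors moves the RR only to (11.2 + 1.56)/(11.2 + 3.12) = 0.89. This stands, and is why the survivor figures should be kept.

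**Conclusion.** The concern holds in conditional form. As written, the rule can declare benefit on the 24-month items and the 3- and 18-month MRI when a drug only turns disabled survivors into deaths, and can suggest harm when it saves severely affected infants. If extra deaths concentrate in severe HIE, as the Background rates make plausible, the crude survivor RR is 0.83 in the unscaled example and 0.87 to 0.89 with scaled rates; the unscaled all-randomised RR is 0.70. All rest on the assumed severity mix and the assumed 20-point rise in severe mortality.

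Three stronger readings are not supported. The documents give no evidence that topiramate raises mortality; that is a scenario only. The first-week MRI should not be grouped with the later assessments, because it loses only deaths before that scan. The primary composite counts deaths and is not affected, so this point does not challenge the main comparison.

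**What to change.** 1. Delete the unconditional statement that an RR below 1 indicates improvement, for the secondary disability items and the MRI comparisons.
2. State the denominator of each item, and do not count an infant who died before the assessment as free of the event.
3. For each item add a death-inclusive analysis over all randomised infants: either death or the impairment, or an ordinal ranking with death as the worst category.
4. Present survivor-only RRs, stratified by aEEG randomisation group, as description, with mortality by arm beside them.

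The cost is wording and some extra analysis; no new data are needed. The drawback is that death-inclusive items are less specific to each impairment and overlap with the primary outcome, so the survivor figures stay in the report.

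### Reading any RR below 1 as neuroradiologic improvement gives contradictory, sometimes wrong-signed, results when the MRI items are isolated-versus-combined lesion patterns

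*Protocol article*

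**What the plan says.** Under Secondary outcomes, MRI findings at three time points (first 7 days, 3 months, 18 months) are to be compared between arms. The classification is: "Brain injuries will be classified as isolated lesions of the white matter (WM), of basal ganglia and thalami (BGT"), with or without the posterior limb of the internal capsule (PLIC), "of cortex (COR), or various combinations of such lesions".

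Under Experimental plan and data analysis, the protocol says "we will evaluate the different distribution of any brain lesions on MRI brain highlighted". It continues: "The RR is calculated for each item studied". The interpretation follows at once: "An RR <1 indicates an improvement of neurological, neurodevelopmental and neuroradiologic hypothermia due to the association-topiramate".

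The article does not define an item. The only MRI lesion categories it lists are those above. It ranks none of them by severity and names no any-lesion or region-by-region item.

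**The concern.** A rule that RR below 1 means improvement works only if having the item is always worse than not having it. That is true of death, epilepsy or any brain lesion. It is not true of an isolated lesion pattern, because an infant can leave that category in two opposite ways: by having no lesion, or by having lesions in further regions as well. Both lower the RR for the isolated pattern, and the rule reads both as benefit.

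The protocol's background makes region-selective effects plausible. It reports that whole-body cooling mainly spared the thalami, basal ganglia and white matter, and that selective head cooling seemed to do more for the cortex. Protection of some regions but not others is what moves infants between combined and isolated patterns.

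At stake is how the imaging part of the efficacy comparison is read. With several patterns and three scan times, a report could contain item RRs that disagree, with nothing in the stated rule to show which to believe. A confidence interval or test would not help, since precision does not correct the direction of the reading.

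**Working it through.** **Inputs.** From the protocol: 32 infants per arm, the pattern classification, one RR per item, and RR below 1 read as improvement. Assumed, because the protocol gives no MRI frequencies: all pattern counts and shares below, and that all 32 per arm are scanned.

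**The plan's own figure.** No figure is given for the MRI analysis. The 32 per group comes from the primary outcome (50% versus 15%, alpha 0.05, power 80%). Two-sided without continuity correction:

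n = [1.96 × √(2 × 0.325 × 0.675) + 0.842 × √(0.25 + 0.1275)]² / 0.35² ≈ 26.9, so 27.

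With continuity correction:

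(26.9/4) × [1 + √(1 + 4/(26.9 × 0.35))]² ≈ 32.4, or 33 rounded up.

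The stated 32 is therefore reproduced to within one infant. It is used here only as the denominator.

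**Algebra.** Let pᵢ and p_c be the control shares with isolated and combined injury.

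- Spread: a fraction h of isolated injuries becomes combined. RR(isolated) = 1 − h, and RR(combined) = 1 + h·pᵢ/p_c. The isolated RR is below 1 for every h > 0.
- Reduction: a fraction f of combined injuries becomes isolated and a fraction g of isolated injuries is prevented. RR(isolated) = 1 − g + f·p_c/pᵢ, and RR(combined) = 1 − f. The isolated RR exceeds 1 only if f·p_c > g·pᵢ.

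**Assumed counts, 32 per arm (none / isolated / combined).**

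| Case | Control | Topiramate | RR isolated | RR combined | RR any lesion |
|---|---|---|---|---|---|
| A. Injury spreads | 8 / 16 / 8 | 8 / 8 / 16 | 8/16 = 0.50 | 16/8 = 2.00 | 24/24 = 1.00 |
| B. Combined becomes isolated | 8 / 8 / 16 | 8 / 16 / 8 | 16/8 = 2.00 | 8/16 = 0.50 | 24/24 = 1.00 |
| C. Half of each injured class moves one step down | 8 / 16 / 8 | 16 / 12 / 4 | 12/16 = 0.75 | 4/8 = 0.50 | 16/24 = 0.67 |

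In A the rule calls the isolated result an improvement although eight infants have more extensive injury. In B the isolated RR is above 1 although eight infants have less extensive injury. In C both RRs point the right way.

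**How often it would be seen.** The setting was a shift like B with f = 0.5 and g = 0, simulated with 200,000 draws at 32 per arm:

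| Control isolated / combined | True RR isolated | Chance observed RR isolated > 1 |
|---|---|---|
| 25% / 37.5% | 1.75 | 93% |
| 25% / 25% | 1.50 | 83% |
| 40% / 20% | 1.25 | 75% |
| 15% / 50% | 2.67 | 99% |

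For comparison, with no shift at all and 25% / 37.5%, that chance is 44%. These are the chances for a pure shift of this size, not a forecast.

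**Non-exclusive items.** Assumed control: 12 none, 6 isolated WM, 2 isolated BGT, 12 WM+BGT. Under topiramate six infants move from WM+BGT to isolated WM: 12, 12, 2, 6.

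- Isolated WM: 12/6 = 2.00
- Any WM: (12 + 6)/(6 + 12) = 18/18 = 1.00
- Any BGT: (2 + 6)/(2 + 12) = 8/14 = 0.57

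The regional items show what happened: white matter unchanged, deep grey matter spared. With the arms swapped, any BGT is 14/8 = 1.75, correctly unfavourable, while isolated WM is 6/12 = 0.50, which the rule would call improvement.

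**The case against.** The link between the two sections is inferred. The protocol never says that an RR is taken on each pattern. The sentence before the rule speaks of a distribution of lesions, which could mean a descriptive table, an any-lesion item or region-by-region items. Under those readings nothing reverses. A condensed article may also leave item coding to the full protocol, and the classification rests on a cited source not available here. This stands as a reason for caution. It does not remove the point, because the article itself fixes the interpretation rule, applies it to imaging, and offers only the isolated-or-combined patterns as MRI lesion items.

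Two stronger readings are tempting, and the documents support neither.

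- A reader might infer that a real reduction in injury would be scored as harm. The protocol states only what RR below 1 means; harm for RR above 1 is an implied converse. In case B the combined item is also read, correctly, as improvement. The result is mixed readings, not a verdict of harm. Case A needs no converse, since there the rule as written gives the wrong reading.
- A reader might infer that an effective drug must push the isolated RRs above 1. Case C shows otherwise.

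Nor may the isolated patterns be called milder in themselves: the protocol gives no severity order, and isolated BGT injury with PLIC involvement is not shown to be less serious than, say, WM plus cortex.

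**Conclusion.** The concern holds as a fault in a stated interpretation rule. On the most natural reading, an RR below 1 on an isolated pattern can mean either less injury or more extensive injury, and the protocol calls both improvement. Where one class gains infants from the other with the uninjured share unchanged, the isolated and combined RRs fall on opposite sides of 1 (0.5 and 2.0 in the illustration). Where isolated lesions are also prevented in sufficient number, the RRs agree and are correctly signed.

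The conclusion rests on two assumptions: that the MRI items are the listed patterns, and that those patterns exclude one another. The sizes rest on assumed counts. The direction under pure spread does not; the direction under reduction depends on whether f·p_c exceeds g·pᵢ.

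The reach is limited. MRI pattern is a secondary outcome in a pilot trial. The primary outcome of death or severe disability and the 32 per group are untouched.

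**What to change.** Amend Experimental plan and data analysis and Secondary outcomes to say that:

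1. MRI RRs are computed on non-exclusive items: any lesion, and WM, BGT, PLIC and COR each scored as involved or not, whatever the other regions show.
2. The reading of RR below 1 as improvement applies only to those items. For each of them a lower RR always means fewer infants with that injury.
3. The isolated and combined patterns are reported by arm as a descriptive table, without the RR reading.

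The any-lesion item alone is not enough: it stays at 1.00 in cases A and B, so the regional items are needed to show changes in extent. A grade by number of regions is not needed for this repair and would impose a severity order that the protocol does not support.

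The cost is about one paragraph. The same blinded MRI reads supply every item, with no further scans, readers or infants.

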### Ethical approval

A three-centre phase II pilot study entitled “Safety and Efficacy of Topiramate in Neonates With Hypoxic Ischemic Encephalopathy Treated With Hypothermia (NeoNATI)” has been approved by the Ethics Committees of A. Meyer University Children’s Hospital, Florence, of University of Pisa and of La Sapienza University, Rome (prot. 276/2010).

Informed consent will be obtained from at least one parent prior to study entry. Parents will be given full verbal and written information regarding the objective and procedures of the study and the possible risks involved.

TPM is considered safe for use in children. Nevertheless, a careful watch will be kept on all study participants with regard to side effects of drug administration. Parents of participants will be made aware of possible side effects. Infants will be monitored in the Neonatal Intensive Care Unit throughout the study period and their clinical condition will be evaluated daily as part of medical rounds. A letter informing the participant and the family doctor as to which study arm the participant had been randomized to will be sent following completion of the study.

In the presence of adverse events, a reduction of dosage will be taken into account.

For ethical and scientific reasons, an interim analysis after the enrolment of half of the newborns, is planned.

